## Abstract

**Background:**

Non-alcoholic fatty liver disease, the most prevalent liver disease in developed countries, remains difficult to manage with no proven safe and effective pharmacotherapy available. While weight reduction is the most commonly practiced treatment strategy, this is difficult to both achieve and/or maintain in the majority. Furthermore evidence-based dietary recommendations to guide the nutritional management of these patients are lacking. Using a randomised controlled trial design, this study compares the effectiveness of the Mediterranean diet to a standard low fat diet in terms of differences in insulin sensitivity, hepatic steatosis and metabolic outcomes in participants with non-alcoholic fatty liver disease.

**Methods:**

Ninety four eligible patients who have non-alcoholic fatty liver disease and who are insulin resistant, will be randomised into either a Mediterranean or low fat diet group for a 3 month intervention period. Insulin sensitivity will be measured on peripheral blood using Homeostatic Model Assessment and liver fat content quantified using Magnetic Resonance Spectroscopy. Both arms will consist of three face to face and three telephone call follow up consultations delivered by an Accredited Practicing Dietitian. The intervention arm focuses on recommendations from the traditional Mediterranean diet which have been tailored for use in the Australian population The standard arm uses the Australian Guide to Healthy Eating and the Australian National Heart Foundation dietary guidelines. Study recruitment will take place at four major metropolitan hospitals in Melbourne, Australia. Data collection will occur at all face to face reviews including baseline, 6, and 12 weeks. A follow up assessment to measure sustainability will take place at 6 and 12 months. The primary end point is improved insulin sensitivity scores at the 12 week time point.

**Discussion:**

This trial aims to demonstrate in a large cohort of participants with NALFD that a Mediterranean diet independent of weight loss can result in significant benefits in liver fat and insulin sensitivity and that these changes are sustained at 12 months. These metabolic changes would potentially lead to reductions in the risk of chronic liver disease, heart disease, type 2 diabetes and liver cancer.

**Trial registration:**

Australia and New Zealand Clinical Trials Register ACTRN: ACTRN12615001010583.

## Background

Non-alcoholic fatty liver disease (NAFLD) and its progressive form, non-alcoholic steatohepatitis (NASH) are among the most prevalent of liver diseases worldwide. Approximately 20 to 30 % of the adult population has NAFLD, making it the most common liver disease in developed countries [1–3]. The incidence is as high as 50–85 % in people with pre-diabetes and diabetes [4, 5], with diabetic patients having a two to threefold higher risk of dying of chronic liver disease, primarily attributable to NAFLD [6]. In addition, NAFLD has been associated with the occurrence of cardiovascular disease (CVD), independent of the classical risk factors [7]. CVD is the leading cause of death in Australia and globally [8]. An estimated 30 % of patients with NAFLD have NASH, which leads to cirrhosis and its complications including, portal hypertensive bleeding, hepatocellular carcinoma and hepatic decompensation [9]. Insulin resistance is strongly implicated in the development of steatosis (fatty liver) and its progression to NASH. The clinically relevant lesion progresses to cirrhosis in 20–30 % of cases and leads to liver cancer in 2–5 % of cases [10]. Currently no proven, safe, effective therapy exists for NAFLD and NASH [11]. Given the increasing prevalence of these conditions and high incidence of associated metabolic comorbidities, the global burden is expected to steadily increase.

Diet is a modifiable risk factor that can potentially be targeted in both the prevention and treatment of NAFLD. Currently no firm dietary recommendations can be formulated in the management of NAFLD because of the paucity of high quality evidence-based data associated with metabolic outcomes. However current data suggests that patients should aim to achieve a 5–10 % weight reduction, reduce saturated and trans fat, limit fructose, limit intake of simple carbohydrates and substitute with complex carbohydrates such as whole grains, fibre and fruits [12–14]. However, weight loss is neither easy to achieve or maintain and weight loss achieved in research trials is not easily replicated in the clinic or real world settings. As such, there is an urgent need for therapies independent of weight loss.

The health benefits of the Mediterranean Diet (MedDiet) have gained popularity in the scientific literature and lay world with respect to being one of the healthiest diets in the world. Its effects are well researched in high quality studies such as PREDIMED and benefits are attributed to a lower incidence of chronic disease including CVD, obesity, dementia, some cancers, and overall mortality demonstrating its safety, palatability and sustainability [15].

Pilot data to support the shift from current dietary therapy to a novel MedDiet intervention of patients with NAFLD has been published by Ryan et al. in NAFLD patients [16]. This study demonstrated a significant improvement in insulin sensitivity and hepatic steatosis with the MedDiet compared to no change in the low fat diet group.

This study, MEDINA (Mediterranean Dietary Intervention study in Non-alcoholic fatty liver disease) aims to replicate the findings of Ryan et al’s pilot study ina larger cohort of participants with NAFLD in a more translatable environment and with assessment of sustainability. The study aims to investigate the effects of adhering to the MedDiet as compared to a low fat diet. We hypothesise that the MedDiet will demonstrate a potential to reverse insulin resistance and reduce fatty liver and that the benefits will be sustained 12 months post study initiation date with maintenance of the diet. We also aim to explore molecular mechanisms at play in the disease process and the interplay with diet.

## Methods

### Study design and outcome measures

This is a 12 week, multi-centre, parallel, randomised controlled trial of a Mediterranean diet versus a Low Fat Diet (LFD) in patients with NAFLD on insulin resistance, hepatic steatosis and Metabolic Syndrome (MetS) risk factors. Enrolment of 94 participants will occur at four sites across metropolitan Melbourne, Australia: Alfred Health, St Vincent’s Hospital, The Royal Melbourne Hospital and Eastern Health. Both the recruitment and intervention are anticipated to take place over a 24 month period. Participants will undergo stratified randomisation according to gender and diabetes status, into either the intervention; MedDiet or the LFD arm. The primary endpoint is the reduction of one unit of homeostasis model assessment of insulin resistance (HOMA-IR) over the 12 week intervention period. Secondary outcome variables include a reduction in intrahepatic lipid accumulation measured by Magnetic Resonance –Spectroscopy (MR-S), normalisation or improvement of alanine aminotransferase (ALT), lipid profile, liver stiffness as measured by transient elastography (Fibroscan®), inflammatory cytokine markers, quality of life measures, anthropometry and body composition, biomarkers of dietary intake and blood pressure.

### Participant recruitment and eligibility

Participants will be recruited from the outpatient Liver Clinics of four major metropolitan University hospitals via referral from the managing hepatologist of potentially eligible participants for screening. Screening will be performed by a trained researcher.

### Inclusion criteria

Participant eligibility includes those aged >18 years who have a body mass index (BMI) between 20 and 39.9 kg/m^2^. Participants must have a diagnosis of NAFLD determined by routine ultrasound or biopsy; insulin resistance based on a HOMA IR score of >2; and at least one elevated serum ALT level (>20 U/L female, >30 U/L male) during the past 6 months. Eligible participants must have no evidence of another form of liver disease.

### Exclusion criteria

Participants will be excluded if they:Refuse or are unable to give informed consent to participate in the study;Are Non-English speaking;Consume on average >140 g/week of alcohol (men and women);Are taking the following medications: immunosuppressants, amiodarone and/or perhexiline;Have had a weight change exceeding 5 kg within 3 months;Are currently following or anticipated to commence a specialised commercially available weight loss diet and/or program (eg. Light and Easy, Optifast etc.);Have a diagnosis of insulin dependent diabetes mellitus or those taking gliclazides;Have a HbA1c score exceeding 8 %;Have a current or prior history of cardiovascular, cerebrovascular or peripheral vascular disease;Have clinically relevant pulmonary, gastro-intestinal, renal, metabolic, hematological, neurological, psychiatric, systemic or any acute infectious disease or signs of acute illness;Are women who are pregnant;Have psychosocial or gastrointestinal (e.g. malabsorptive conditions e.g. coeliac)Have contraindications included bulimia nervosa, substance abuse, clinically significant depression, or current psychiatric care;Have had a recent (within 3 months) of change in dose/regime or introduction of vitamin E, C or high dose vitamin D (>3000 IU), fish oil or probiotics.

### Timeline of assessments

All participants will complete a face-to face dietary and lifestyle assessment and consultation, anthropometry and biochemistry at baseline, mid-intervention (6 weeks) and end-intervention (12 weeks). Participants from both groups will also undergo phone call follow up reviews at weeks 2, 4 and 9. All participants will undergo assessment of hepatic steatosis with MR-S and fibrosis with Transient Elastography; Fibroscan® at baseline and end-intervention. Dual-energy X-ray absorptiometry (DXA) scans are voluntary and will assess body composition. All participants will be followed up face to face at 6 and 12 months after study recruitment to determine maintenance and sustainability of the diet administered and subsequent changes in imaging and biomarkers. Please refer to Table 1 for the schedule of measures.

**Table 1 Tab1:** Schedule of measures

Variable	Instrument	Time point				
Self-reported		Baseline	Mid intervention	End intervention	6 month	12 month
Diet intake	Food Frequency Questionnaire (FFQ), 3- day food diary	X	X	X	X	X
Diet compliance	PREDIMED checklist (low fat or MD)	X	X	X	X	X
Physical activity	Active Australia Questionnaire	X	X	X	X	X
Quality of life	SF-36	X	X	X	X	X
Medications and supplements	Self-report	X	X	X	X	X
Smoking status	Self-report	X				
Ethnicity	Self-report	X				
Medical history	Self-report and clinical records	X	X	X	X	X
Anthropometric and clinical						
Weight, height, waist and hip circumference, neck girth		X	X	X	X	X
Blood pressure		X	X	X	X	X
Whole body composition	Bioelectrical Impedance Analysis (BIA), DXA (subgroup)	X	X *(NO DXA)*	X	X *(NO DXA)*	X
Intrahepatic lipids	MR-S	X		X		X
Liver fibrosis	Fibroscan	X		X		X
Pathology						
	Venous blood sample (fasting)	X	X	X	X	X
	First morning urine sample	X	X	X	X	X
	Buccal swab	X				

### Study procedure

#### Screening assessment

Prospective participants will undergo a thorough screening questionnaire administered face-to-face by a trained researcher. Once considered eligible, participants will undergo computer generated randomisation stratified to gender and diabetes status completed by the statistician. Participants will be allocated into either the LFD or the MedDiet arm of the study and booked in for their initial appointment.

Randomisation will control for equal distribution of key characteristics that may confound between group comparisons and will be assessed by analysis of baseline data.

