#### Low fat diet

The LFD group will follow the same structure as the MedDiet arm with three face to face consultations at baseline, 6 weeks (mid intervention) and 12 weeks (end of intervention). There will also be the same number of phone call follow ups at weeks 2, 4 and 9. The education and resources provided will be determined by the APD running the consultations and these will involve what would normally be provided in a typical outpatient dietetic consult. This will include based on the Australian Guide to Healthy Eating with an emphasis on portions, low fat options and cooking methods. Participants will also be given a supermarket gift voucher to purchase some of the suggested food items.

Breakfast is also provided on the day of all face to face appointments (Jalna © and Carmen’s ©).

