### Statistical analysis

Intention-to-treat (ITT) principle will be used to analyse and compare the intervention and control groups. As per ITT principle, for the purpose of statistical analyses, all participants will retain their randomised (allocated) group, regardless of the actual treatment received. T-test will be used to examine the effectiveness of randomisation by comparing baseline characteristics across the two groups. If data are not normally-distributed, nonparametric Kruskal-Wallis test will be used instead.

For quantitative endpoints (e.g., HOMA-IR), linear mixed-effect models will be used to compare the intervention and control group. If normality assumption is not fulfilled, suitable transformation (e.g., log) will be performed on the response variable to ensure the assumption is met. For binary endpoints (e.g., improvement in lipid profile >20 %), mixed-effect logistic regression for longitudinal data will be used. In both cases, data from all participants, including those who withdraw after baseline, will be retained for analyses. When required, potential confounders (e.g., age, BMI) will be adjusted for by including them as additional covariates in the models.

When multiple hypothesis testings are performed (e.g. with SNP data), Holm’s procedure (Holm, 1979) will be used to control the familywise error rate. All statistical analyses will be performed using 5 % significance levels. R version 3.1.1 (www.r-project.org) and STATA version 12 will be used to conduct the statistical analyses.

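### Participants are allocated before the baseline visit, so the scheduled Table 1 baseline measures are taken after randomisation in an open diet trial

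*Protocol article*

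**What the plan says.** The Screening assessment section sets the order. After a screening questionnaire, "Once considered eligible, participants will undergo computer generated randomisation stratified to gender and diabetes status completed by the statistician". The next step is: "Participants will be allocated into either the LFD or the MedDiet arm of the study and booked in for their initial appointment".

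The Low fat diet section, which says that both arms share one structure, lists "three face to face consultations at baseline, 6 weeks (mid intervention) and 12 weeks (end of intervention". The Timeline of assessments puts measurement and dietary advice at the same point: "All participants will complete a face-to face dietary and lifestyle assessment and consultation, anthropometry and biochemistry at baseline". Imaging is listed likewise: "All participants will undergo assessment of hepatic steatosis with MR-S and fibrosis with Transient Elastography; Fibroscan® at baseline and end-intervention". Table 1 also marks a compliance form at baseline, labelled "PREDIMED checklist (low fat or MD". The Dietary and lifestyle section describes this form as tailored to the diet of each arm.

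Some values must exist before randomisation. The Inclusion criteria require a BMI range and "insulin resistance based on a HOMA IR score of >2; and at least one elevated serum ALT level", and the Exclusion criteria set an upper limit on HbA1c.

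The Statistical analysis section keeps everyone in the allocated group, uses t-tests on baseline characteristics to judge the randomisation, and plans mixed-effect models. It adds: "In both cases, data from all participants, including those who withdraw after baseline, will be retained for analyses".

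**The concern.** A baseline value is useful because allocation cannot have affected it. Here the order removes that guarantee for every measure that Table 1 schedules at baseline. The diets are delivered by counselling and supplied foods, so participants cannot be blinded once they know their arm. Anyone who learns it before the visit may start changing what they eat, or may answer diet, activity and quality-of-life questions differently.

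Three things are at stake:

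- **Effect estimates.** The primary endpoint is framed as a reduction in HOMA-IR over the 12 weeks, and several secondary outcomes are framed as reductions or improvements. A reference value that has already moved distorts such estimates. For a real early diet change the pull is towards no difference. For self-report it could go either way.
- **The check of randomisation.** A baseline difference between arms could reflect chance or a response to allocation, and the planned t-tests cannot tell these apart.
- **Early loss.** Someone who dislikes the assigned arm can withdraw before anything on the study schedule has been measured. Such loss may differ by arm.

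**Working it through.** The point concerns the order of events, and the article gives no figure for it. I first set the sections side by side and then show how the size scales under stated assumptions.

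**1. Order of events**

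- Screening questionnaire, then eligibility, then randomisation by the statistician, then allocation and booking of the initial appointment (Screening assessment).
- The first of the three face-to-face consultations is at baseline (Low fat diet).
- Diet and lifestyle assessment, consultation, anthropometry and biochemistry take place at baseline (Timeline of assessments).

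No other appointment is described between allocation and baseline, so the initial appointment is, by strong inference, the baseline visit.

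**2. Is the arm known by then?** The article does not say when participants or assessors are told. The arm-specific checklist marked at baseline suggests that the arm is already in use: if there are two versions, staff need the allocation to choose one, and the form itself can reveal the arm. The three-day food diary is also a baseline item. If it is handed in at the visit, it was kept after allocation.

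**3. Which values precede allocation?** HOMA-IR, BMI, ALT and HbA1c, because eligibility depends on them. MR-S, Fibroscan, diet records, activity and SF-36 are not eligibility measures. Table 1 schedules its own fasting blood sample at baseline, and nothing says that screening values take its place.

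**4. Effect on the estimate.** Let D be the true between-arm difference at 12 weeks, and let a fraction f of it already be present at the measured baseline. Let b be the slope of the 12-week value on baseline.

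- Change from baseline: D − fD = (1 − f)D
- Baseline-adjusted: D − b·fD = (1 − bf)D
- Unadjusted 12-week contrast: D

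With the article's D = 1.0 HOMA-IR unit (Sample size), and f and b assumed:

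| f | Change score | Adjusted, b = 0.5 | 12-week only |
|---|---|---|---|
| 0 | 1.00 | 1.00 | 1.00 |
| 0.1 | 0.90 | 0.95 | 1.00 |
| 0.2 | 0.80 | 0.90 | 1.00 |

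**5. Early loss.** The Sample size section gives 94 participants and a 20% allowance: 94 × 0.20 = 18.8 people. Assume that 3% to 10% leave between allocation and the visit:

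- 94 × 0.03 = 2.8 people, and 2.8 / 18.8 = 15% of the allowance
- 94 × 0.10 = 9.4 people, and 9.4 / 18.8 = 50% of the allowance

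These people would have no baseline-visit or follow-up outcome, so a mixed model would have nothing to use for them unless a screening value were brought in.

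**The case against.** The strongest reply has five parts.

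- **Pre-allocation values exist.** A reader might infer that every baseline measure follows randomisation. The eligibility criteria rule that out: a HOMA-IR value, with BMI, ALT and HbA1c, must be available first. This stands and limits the point to the scheduled Table 1 measures. It does not remove the point, because nothing makes the screening values the analysis baseline.
- **Intention to treat is not breached.** A reader might infer from the retention sentence that people lost before the first visit are dropped by rule. The text does not support that. Participants keep their allocated group, and the word including widens the set. This stands in full. What remains is a practical consequence of the visit order: such people have no visit data.
- **Disclosure is not dated.** The article does not say that participants know their arm before measurement, gives no waiting interval, and describes no dietary advice before the visit. This stands, so the bias is possible and not shown. The order nevertheless leaves it open, and the baseline checklist makes early knowledge more likely.
- **Not every estimate is exposed.** The trial is sized on the 12-week difference between groups, and an unadjusted 12-week contrast is untouched by a shifted baseline. The most exposed items, self-reported diet, activity and SF-36, are not primary. This also stands. However, the primary endpoint is worded as a reduction over the intervention period, which invites a change or adjusted analysis.
- **An article condenses.** Details of disclosure could be in the full protocol. But the article does state an order, and no later analysis plan can recover a baseline measured before allocation.

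**Conclusion.** The point holds for the scheduled baseline measures. They follow allocation in an open diet trial, so they can be influenced by knowledge of the arm, and the baseline comparison is a weaker check of randomisation than the protocol assumes.

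The size cannot be determined from the article. A change-score estimate loses the fraction f of the effect already present at baseline. A baseline-adjusted estimate loses bf, and an unadjusted 12-week contrast loses nothing. The values of f and b, and the 3% to 10% early loss (about 3 to 9 of 94 people), are assumptions that show scale only.

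The conclusion rests on two readings: that the initial appointment is the baseline visit, which is a strong inference, and that the arm is or can be known by then, which the article does not state outright. It does not extend to the screening values or to any stated exclusion from the intention-to-treat analysis. The order should be changed because the remedy is cheap and the problem cannot be repaired at analysis.

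**What to change.** In the Screening assessment section, reverse the order. Book eligible participants for baseline measurement, complete the Table 1 baseline items (fasting blood, MR-S, Fibroscan, food diary and questionnaires, anthropometry), and have the statistician release the allocation only then, immediately before the first dietetic consultation. Stratification is unaffected, since gender and diabetes status can be recorded at screening.

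If the compliance checklist has two versions, the baseline version can no longer be chosen by arm before release. Either everyone completes both, or this one form is filled in after release and reported as such.

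People who fail to attend for baseline would then never be randomised, and those who withdraw on learning their arm would at least have baseline data. The definition of the intention-to-treat set needs no change for this purpose.

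The cost is minor scheduling. The dietitian must be ready to deliver either arm on the day, and imaging may have to be booked before the consultation, possibly as a separate attendance. No new outcome measures or staff are needed.

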### Dietary interventions

#### Mediterranean diet

The intervention is based on a traditional MedDiet as described in Keys et al. in the seven countries study and the macro and micronutrient compositions described in previous MedDiet controlled trials [17–20]. The diet is rich in plant based foods including vegetables, whole grains and fruit with the main added fat being extra virgin olive oil. The diet emphasises increased legumes and raw unsalted nut intake and oily fish. Moderate amounts of fermented dairy and poultry with small amounts of red meat and homemade sweets. The diet comprises of 44 % fat (>50 % monounsaturated), 36 % carbohydrate and 17–20 % protein and up to 5 % alcohol. The diet was designed to be easy to follow and sustainable with an ad libitum approach focusing on what should be consumed rather than what to avoid. All changes to diet and lifestyle will be administered to participants by an Accredited Practising Dietitian (APD) who is able to tailor the diet to cultural and personal preferences through recommendation of nutritionally appropriate alternatives where necessary.

All participants will be provided with written resources specifically designed to explain the MedDiet and how it can be successfully followed and adhered to. These resources include a food pyramid, healthy eating guidelines and tips, meal plans, recipes in the form of; The Mediterranean Diet recipe book by [name] (ISBN 9781742610825), a shopping list, ‘no cooking’ meal options and label reading. Participants will also be asked to set individual goals at each session which will be used as a focal point for subsequent phone call follow ups and appointments and will assist with having directed changes and maintaining motivation. Participants will also be supplied with extra virgin olive oil (Cobram Estate©) for the duration of the intervention and some MedDiet specific food items such as nuts (Almond Board Australia), canned legumes and fish (Simplot Australian Pty Ltd and HJ Heinz©) which are aimed at providing practical and convenient examples of what items constitute a MedDiet. Breakfast is also provided on the day of all face to face appointments (Jalna © and Carmen’s ©).

